## Abstract

**Background:**

Alarming rates of unhealthy alcohol, non-prescription drug, and tobacco use highlight the preventable health risks of substance abuse and the urgent need to activate clinicians to recognize and treat risky use. Screening, brief intervention, and referral to treatment (SBIRT) is an efficacious and effective processes to identify, reduce and prevent risky use of substances. This paper describes a study protocol testing implementation of a toolkit to enhance use of SBIRT in acute care settings to recognize and address patient risky alcohol, drug, and tobacco use.

**Methods:**

This study uses a phased cluster randomized mixed method design to test nurse-led implementation of an SBIRT toolkit on one medical-surgical unit at 14 acute care hospitals (critical access, community and academic health centers). Medical surgical units will be randomly assigned to implement the SBIRT toolkit (engagement and communication, assessment, planning, training, and evaluation tools) or a wait-list usual care control group that begins implementation 6 months later. Primary endpoints are documentation of SBIRT delivery in randomly selected electronic medical records at baseline, 6 months and 12 months after group 1 implementation (61 records per unit per time period, N = 2562). Two surveys will be administered to unit nurses: smoking cessation activities will be assessed at baseline and SBIRT use will be assessed on randomly-selected days after implementation. In addition, site coordinators will complete a baseline capacity assessment, an implementation fidelity survey post-implementation, and a structured interview at the end of the study. Multilevel mixed-effects effects logistic and linear models will be used to analyze use of SBIRT and cost outcomes.

**Discussion:**

This study will guide subsequent SBIRT implementation, dissemination, and spread across rural, community and urban healthcare systems throughout the state and beyond. The long-term objective is to activate clinicians to recognize, intervene and refer people with risky substance use to improve health and decrease substance use disorders.

*Trial registration* ClinicalTrials.gov NCT03560076

## Background

According to the World Health Organization, mental health and substance use disorders will surpass all physical diseases as a major cause of disability worldwide by 2020 [1]. In the United States, the annual total estimated societal cost of substance use disorders is $510.8 billion [2]. The negative outcomes and costs associated with substance use are not exclusive to any specific substance. For example, alcohol use is linked to significant economic and health costs on a global scale [3]. It is often a contributing factor in homicides, suicides, crimes (violent, including homicide, and non-violent), motor vehicle collisions (non-fatal and fatal), and unintentional injuries to the drinker and others in his/her environment [4]. Heavy drinking can lead to a pattern of abuse and/or dependence that is often associated with other harmful behaviors such as cigarette smoking, unsafe sex, and illicit drug use [5]. Even lower levels of drinking, while potentially asymptomatic, are associated with health risks [6].

In addition, despite a steady decline in smoking rates among the general population over the past several decades, tobacco use remains the primary known preventable cause of morbidity and mortality in the United States, resulting in an estimated 480,000 deaths annually from tobacco-attributable diseases [7]. Quitting smoking has a greater impact on cardiovascular risk than changes in blood pressure, weight, physical activity, or lipids [8]. Finally, and of particular relevance to the national public health and medical infrastructure in the United States, the rate of non-medical prescription pain reliever use reported in 2014 by US residents between the ages of 18–25 was 2.8% [9]. Further, between 2004 and 2009, emergency department visits increased 98.4% in the US related to non-medical use of prescription drugs [10]. These data have meaningful implications for the US healthcare system. Over 36.5 million adults are admitted annually to acute care hospitals in the US [11]. In such settings, approximately one-third of adult patients screen positive for high-risk drinking or drug use [12].

One promising public health response to this problem is screening, brief intervention, and referral to treatment (SBIRT), which is a comprehensive, integrated approach to the delivery of early intervention and referral to treatment services for persons at risk for or with substance use disorders and/or tobacco use and dependence [13]. Rather than a specific, individual service, SBIRT is a patient care framework based on identifying risk via validated screening tools, intervening on that risk in a manner that is clinically appropriate, and referring to specialty treatment when the risk cannot be managed on-site [14]. Data from a large cross-site evaluation from diverse healthcare sites (n = 754,525) indicate that most patients who screen positive are recommended for a brief intervention (BI 68.8%), followed by brief treatment (BT 14.0%) and referral to specialty treatment (RT 17.2%) [15]. However, SBIRT screening in hospital settings tends to identify both a higher frequency of positive screens for alcohol and increased severity level of those screening scores, relative to outpatient primary care, indicating greater likelihood of patients needing referral [16, 17].

The evidence basis for SBIRT is complex and varies considerably by type of substance, activity, and severity of use. Brief interventions (BI) for unhealthy alcohol use (‘misuse’) are supported by a systematic reviews [18–20] as well as the largest SBIRT evaluation study to date [15]. Alcohol BIs have also demonstrated efficacy for underage drinkers in the ED [21]. However, alcohol BI does not appear to be efficacious for very heavy or dependent users [22]. Further, a recent meta-analysis found no evidence that BI, naturally results in engagement with alcohol-related care [23], though other researchers have disputed this claim [24]. Few SBIRT studies focus specifically on outcomes from referral to treatment (RT) for alcohol [25], sometimes due to difficulty disentangling the type of service provided [26], though the cross-site evaluation from SAMHSA’s SBIRT initiative reported a moderate/large effect for RT [15]. Due to this deficit in the literature, one research team recently conducted a proof-of-concept study for their alcohol RT, yielding promising results for patient engagement with treatment post-SBIRT [27].

SBIRT for tobacco use provides a variety of intervention types ranging from minimal interventions (brochures) to BIs, nicotine replacement therapy (e.g., nicotine patches), and quit line referral. Evidence for these components has generally supported moderate effects on tobacco abstinence, especially for BI or BI with nicotine replacement [7, 28–33]. Some of the research indicates that even minimal tobacco-centric interaction (less than a BI) may have an effect on abstinence [29]. The specific effects of any given component or mixture of components continue to be under investigation, such as in a recent (2018) 16-arm factorial study protocol of tobacco SBIRT focusing on BI, nicotine replacement, quit line referral, and smoke-free text messaging [34].

However, extant evidence supporting SBIRT for other substances is less well established. Some studies and reviews support SBIRT for other substances [14, 35–39]. However, other recent studies found no evidence of efficacy for BI for other substances [40–43], no evidence that BI for other substances reduces negative consequences of drug use [44], and no evidence that BI [43, 45] or RT [42] for other substances increases receipt of treatment. A recent meta-analysis on this subject concluded that the current evidence basis is generally insufficient to make a determination [46]. However, DiClemente’s review of reviews did find support of motivational interviewing (MI) for marijuana, while retaining the perspective of insufficient evidence for other substances (e.g., methamphetamine and opiates) [18]. A recent, innovative modification of SBIRT, called STIRT (screening, treatment initiation, and referral to treatment), included revised protocols and medication-assisted treatment for opioid dependent patients. In a randomized trial, the authors reported increased engagement in opioid treatment and abstinence at 30 days compared to traditional SBIRT and control groups [47].

The SBIRT process is a complex clinical process encompassing multiple components and activities, each of which are often not documented thoroughly, resulting in a body of literature that can be difficult to interpret. O’Donnell and colleagues identified a variety of papers pointing to a ‘lack of training or suitable intervention materials’ as one of several implementation-level barriers to SBIRT [48]. Findings in the SBIRT literature are also mixed, and differentials in implementation strategies may also account for some of the variance in SBIRT trial outcomes [18, 46]. One clear conclusion that can be drawn is that there is a need for randomized trials that thoroughly describe and test specific implementation methods. As a result, this proposed study will examine the impact SBIRT implementation on processes of care across rural, community and urban acute-care hospitals

In particular, this project challenges and seeks to shift current clinical practice paradigms within hospitals by examining the process outcomes associated with a standardized SBIRT process and workforce training toolkit for hospital nurses. Recent research has supported SBIRT training for nurses both as part of academic curricula [49, 50] and as part of quality improvement [51]. The extant patient flow within the hospital system selected for this trial has been responsive to the 2006 Institute of Medicine recommendation to coordinate mental health and substance use services with general health care [52]. But even though hospitalized patients are asked about their substance use on admission, validated screening tools are rarely used, brief interventions are often not conducted, and referrals for treatment are not completed. A hospital admission offers an opportunity for nurses to identify and intervene with patients who are currently using substances at a time when they are already seeking professional care. The health system is therefore ideal for a cluster randomized mixed method approach testing the effectiveness of a toolkit on implementation of SBIRT.

Our prospective study is innovative and promising on multiple levels. It is likely that results will provide information that will support the standardization of both the SBIRT processes and mechanisms of workforce training to address a significant behavioral health problem (substance use) that can be deployed across the health system. This includes both the consistency of inpatient hospital screening and brief intervention and advancing community partnerships for referral to treatment and assessing long-term outcomes. As observed in prior literature, many complexities in interpreting current SBIRT literature result from non-standardized implementation and effectiveness efforts. Therefore, studying implementation is a crucial aspect of the protocol. This approach: (1) utilizes a conceptual framework that maximizes facility engagement in the adoption and implementation of SBIRT; (2) creates buy-in from key stakeholders through the use of a train-the-trainer approach; (3) generates outcome data to facilitate future innovations in practice; (4) produces a SBIRT toolkit with procedures, tools, instruments, implementation guide, and resources to disseminate and sustain SBIRT use; (5) employs an interprofessional team of researchers, educators, and clinicians; and (6) facilitates the adoption of SBIRT across the health system.

Our proposed study partners with a large health system in Indiana and aligns with the State of Indiana Substance Abuse Prevention and Mental Health Promotion Strategic Plan (2012–2017) [53] by implementing SBIRT to improve the identification of people with at risk drug, alcohol or tobacco use, brief interventions and referral to treatment (when indicated). The short-term goal is to inform SBIRT implementation methods for use across rural, community and urban settings. The long-term goal is to develop an SBIRT toolkit with procedures, tools, instruments, implementation guide, and resources to disseminate and sustain SBIRT use to improve access to quality care and outcomes for people that use tobacco, non-prescription drugs, and/or drink an unhealthy amount of alcohol.

The purpose of this study is to examine SBIRT implementation methods across rural, community and urban acute hospital settings. The first aim is to test if implementation of SBIRT improves care delivery and referral of hospital inpatients currently using tobacco, alcohol or non-prescription drugs. The second aim is to evaluate the cost of SBIRT implementation and delivery for the healthcare system.

In US acute care settings, an estimated 1.8 million annual inpatient stays are primarily due to a behavioral health or substance use disorder [54], despite concerted national efforts to reduce the prevalence and incidence of these risky behaviors. There remains an urgent need to advance behavioral health care practices using sophisticated and deliberative approaches to implementation. As this section has demonstrated, the phased cluster randomized approach of SBIRT described here is the next step to advance knowledge about how best to implement SBIRT and if implementation improves use of the SBIRT process moving forward.

## Methods

### Conceptual framework

The Model for Considering the Determinants of Diffusion, Dissemination and Implementation of Innovations in Health Services Delivery and Organization guides this study [55]. This model frames what is known about the adoption of innovations within organizations and guides successful implementation of innovations. The foundation for the conceptual model is based on a narrative synthesis of theory and research that guides effective implementation of innovations in organizations. No one intervention is always effective, and interventions are likely to be more effective if based on assessment of barriers, use multiple strategies, and are system focused [55].

*Antecedents* are attributes of the hospital, such as structural aspects and leadership support that foster incorporation of new evidence, making the organization receptive to change. *Readiness* is the organization’s receptiveness to change, including support and advocacy for the change and dedicated time and resources. Antecedents and readiness are determined through an organizational assessment. *Adoption and/or assimilation* represent the process of incorporation of new evidence into practice. This study includes SBIRT training and nurse SBIRT knowledge (test) and competency (skill validation). *Implementation* is the actual use of the new evidence. In this study, implementation includes the use of SBIRT (survey randomly selected days) and smoking cessation counseling (Smoking Cessation Counseling Scale). *Consequences* are the result or outcome of adoption of new evidence. In this study, the consequences are SBIRT documentation included in the Electronic Medical Record (EMR) and patient follow-up if they are referred for treatment [55].

### Description of intervention

This study protocol will incorporate standardized education on SBIRT through a train-the-trainer approach. Registered Nurse site coordinators from each hospital will receive 8 h of training on the SBIRT process, system strategies to facilitate organizational uptake, and how to teach SBIRT to others. Study investigators will develop this training. The training will be informed by information from the Substance Abuse and Mental Health Services Administration’s public health model of universal screening, early intervention, and treatment for people who have problematic or hazardous alcohol, drug, or tobacco use and dependence, as well as content from the Indiana Prevention Resource Center and Institute for Research on Addictive Behavior. After the site coordinator training is complete, site coordinators at each facility will train additional clinical nurses in SBIRT and develop a referral process specific to their organization’s needs and resources. The site coordinators may also partner with additional staff within their hospital, including social workers and respiratory therapists, to encourage widespread adoption. The site coordinators will partner with unit leaders at each facility to decide how many additional clinical nurses will receive SBIRT training and which employees will receive training. These training interventions are reproducible, publically available, and do not require direct control from the research team. During training, the site coordinators will receive a toolkit that includes the standardized education, engagement and communication tools, assessment tools, planning tools, and evaluation tools to assist with implementation at their facility.

In addition to the toolkit and preparation of site coordinators, the investigators will use several strategies to facilitate implementation. Investigators will provide ongoing consultation to the site coordinators about SBIRT and implementation. Each month, the investigators and site coordinators will participate in a team meeting to discuss implementation barriers and facilitators. Site coordinators will be able to share tools they have developed and strategies they have used to promote implementation. Investigators will encourage adaptability of the intervention to the organizational context while preserving fidelity. The investigators may also make site visits to support implementation of SBIRT and SBIRT education. At the completion of the study, the site coordinators and investigators will work together to enhance the toolkit that was provided during training.

### Study subjects

This study will be conducted at a large healthcare system in the Midwest. Table 1 includes a description of the hospital sites, type and bed size. The hospital sample includes four community hospitals, four academic health centers, and six critical access hospitals with bed size ranges from 15 to 858 beds.

**Table 1 Tab1:** Hospital characteristics by type (N = 14)

	N	Bed range	Mean beds
Academic Health Centers	4	38–858	413
Community Hospitals	4	127–375	214
Critical Access Hospitals	6	15–25	23

### Study design and sample

A phased cluster randomized mixed methods design will be used for this study. Each hospital within the healthcare system is eligible to participate, and the chief nursing officer of each hospital (N = 14) submitted a letter of support for the study. One medical surgical unit within each hospital will be selected by the nurse executive to participate. This selection will be based on the nurse executive’s assessment of the nursing unit capacity to participate in the study and implement a change in practice.

A computer-generated allocation based on a stratified random sampling approach using STATA will be used to randomize hospitals into an intervention or wait-list usual care control group. Prior to randomization, hospitals will be stratified by type (academic health center, community hospital, or critical access hospital). Allocation to the intervention or wait-list usual care control groups will be based on cluster, and participants will be notified of their cluster allocation. Participants in the control group will provide the usual care that is standard for that facility, and then the site coordinators will receive the intervention 6 months after participants in the intervention group (Table 2).

**Table 2 Tab2:** Study design

	Collect pre-data	Intervention		Collect 6-month data	Collect 12-month data
Group 1 (Intervention Group)	0_1_	×		0_2_	0_3_
Group 2 (Wait-List Usual Care Control Group)	0_1_		× (6 months after Group 1)	0_2_	0_3_

All hospitals will receive the intervention. Group 1 (n = 7) hospitals will participate in the implementation intervention first, with Group 2 (n = 7) following 6 months later. Using this phased approach allows for comparisons between a control and intervention group, as well as within hospital changes longitudinally, and ensures there are no ethical concerns related to withholding the SBIRT implementation.

### Data sources

To evaluate SBIRT implementation, several data sources will be used as summarized in Table 3. To assess antecedents to change and readiness for change, the site coordinators will complete a baseline assessment of their hospital for structural capacity (e.g., buy in of stakeholders), staff capacity (e.g., staff competencies), organizational support (e.g., leadership support), technical capabilities (e.g., access to technology), and fiscal capacity (e.g., nurse staffing resources). The qualitative and quantitative baseline assessment was developed by the investigators and will be used to identify areas that need to be addressed before implementation of the study. The site coordinators and investigators will use this data to develop a facility-specific plan to address gaps prior to implementation.

**Table 3 Tab3:** Conceptual framework concepts and operationalization

Concepts	Operationalized	Timing
Antecedents	Organizational attributes (SC)	Program development
Readiness	Attributes of nurses (RN)	Before implementation
Adoption	SBIRT Knowledge (SN)	Post training
	Brief Intervention Adherence and Competency Scale (observation of SN by SC)	Post training
Implementation	Smoking Cessation Counseling Scale (RN)	During implementation
	SBIRT Use and time estimates for each component (SN)	Post implementation, 5 randomly selected days
	Implementation fidelity assessment survey (SC)	Post implementation
	Monthly worksheet (SC)	Continuously
Consequences	SBIRT component documentation in medical record (electronic data abstraction and SC manual data abstraction)	Baseline, 6, and 12 months
	Time estimates for each component delivery (SN)	Post implementation, 5 randomly selected days
	Training details (e.g., number trained, meeting time, administrative time, etc.) with implementation fidelity assessment survey (SC)	Post implementation
	Barriers, facilitators, lessons learned through interviews (SC)	Post implementation End of data collection

*SC* site coordinator, *RN* All direct care nurses on study unit, *SN* all trained nurses

To assess adoption and assimilation at the completion of SBIRT training, site coordinators and direct care nurses will complete a 10-item test constructed for this study to assess knowledge about screening tools, motivational strategies, and referral tools. In addition, competency will be assessed using the Brief Intervention Adherence and Competence Scale [56]. These data will be used to evaluate training and verify SBIRT knowledge and competency.

Actual implementation will be assessed using several strategies. Each month, site coordinators will complete a qualitative and quantitative monthly worksheet developed by the investigators that includes information about the time spent on implementation, changes in care processes, barriers and facilitators to implementation, and lessons learned. On five randomly selected days, site coordinators will collect quantitative data regarding SBIRT use. After each patient admission on the randomly selected days, the direct care nurse or site coordinator will complete a survey regarding fidelity to the different components of SBIRT and the time required to complete SBIRT for that patient. Site coordinators will also complete a survey regarding implementation fidelity. This quantitative and qualitative survey includes questions about the number of nurses trained in SBIRT and actions taken to support SBIRT implementation. Finally, all direct care nurses on the study units (including nurses who did not receive training in SBIRT) will be invited to complete the Smoking Cessation Counseling Scale [57–59]. This survey assesses the extent to which clinicians comply with evidence-based smoking cessation guidelines. Data from the monthly worksheets, SBIRT use assessment, implementation fidelity assessment, and smoking cessation counseling scale will be reviewed by the investigators at the completion of data collection. This information will inform feedback to site coordinators, identify barriers and facilitators to implementation, and inform potential modifications to implementation strategies.

The consequences of SBIRT implementation include the delivery of SBIRT components and the costs of implementation. Delivery of SBIRT components will be measured by the documentation of screening, brief intervention, and referral to treatment for alcohol, drugs, and tobacco, individually and combined. These data will be based on the Joint Commission Quality Measures for alcohol, drug, and tobacco use [60]. The components of SBIRT will be documented in the medical record by healthcare providers who complete the screening, brief intervention, and referral to treatment. All hospitals use the same electronic medical record system. Sixty-one medical records at each site will be randomly selected through automated processes. Inclusion criteria are adult (≥ 18) patients admitted and discharged from units selected for participation in this study within data abstraction periods (baseline, 6 months and 12 months). De-identified data will be abstracted using an electronic data abstraction report. Automated data abstraction will be validated via comparison of electronic and manual data abstraction in a sub-sample of records at each hospital. If required, the site coordinators will conduct the medical record review manually. We will collect data regarding the number of patients screened for alcohol, tobacco, and drugs using a validated tool, and the percentage of patients who screened positive for each substance and then received a brief intervention and/or referral to treatment. The costs of implementation will be assessed using the monthly worksheets completed by the site coordinators and the SBIRT use reports. Data regarding care delivery and costs of implementation will be assessed. At the completion of the study, site coordinators will complete a semi-structured interview to describe their experiences as well as barriers and facilitators of implementation.

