### Statistical analysis

A sample size calculation was conducted to determine the number of medical records needed in each of the 14 study hospitals, to achieve an 80% power at an alpha level of 0.05 to address the quantitative aims of the study while taking the clustered randomization into consideration [61, 62]. Sample size calculations were based on an intracluster correlation of 0.03. In case intracluster correlation is lower than 0.03, our statistical tests provide an even larger statistical power. For the between-group comparisons regarding the binary outcomes of Aim 1, detecting an absolute difference in a proportion between the two groups of 16% with an at least 80% power, using a Z-statistic that accounts for the intracluster correlation, requires 61 medical records per hospital. Based on this sample size for each observation time-point, we are also sufficiently powered to test for within group changes in the control group (post-intervention vs pre-intervention) since within-group comparisons are expected to have a larger power compared to between-group comparisons. Sample size calculations were conducted using the PASS 13 software.

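### Brief intervention and referral are stated as percentages of screen-positive patients, a group formed after randomisation by the screening the toolkit is meant to raise and smaller than the 61 records per unit behind the power claim

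*Protocol article*

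**What the plan says.** The Abstract makes documented SBIRT delivery in randomly selected records the primary endpoint, with 61 records per unit and period. Under Data sources, the records are a random sample of all adults admitted to and discharged from the unit. Screening is to be collected as a number of patients screened with a validated tool. Brief intervention (BI) and referral to treatment (RT) are to be collected as "the percentage of patients who screened positive for each substance and then received a brief intervention and/or referral to treatment".

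On current practice, the Background says that "validated screening tools are rarely used, brief interventions are often not conducted, and referrals for treatment are not completed". On prevalence in acute care hospitals, it says that "approximately one-third of adult patients screen positive for high-risk drinking or drug use".

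The sample size paragraph in Statistical analysis sets out "to achieve an 80% power at an alpha level of 0.05", with "Sample size calculations were based on an intracluster correlation of 0.03". The scope of the calculation is worded as follows: "For the between-group comparisons regarding the binary outcomes of Aim 1". The stated conclusion is that a 16-point absolute difference, at 80% power or more, "requires 61 medical records per hospital". The paragraph does not separate screening from BI or RT. Intention-to-treat is defined there at unit level: every unit stays in whatever its adherence. The Aim 1 section names a multilevel logistic model and does not state which records enter it for BI and RT.

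**The concern.** Two problems follow if BI and RT are compared between arms among screen-positives.

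**Comparability.** The denominator depends on who was screened, and raising screening is part of what the toolkit does. At 6 months the wait-list units would contribute few screen-positive patients, plausibly the obvious cases. The toolkit units would contribute more, including milder cases. Randomisation balances the units' patients, not these subsets. The before-after comparison within units has the same weakness, because screening changes over time. Keeping every unit in the analysis does not help, and neither does covariate adjustment aimed at chance imbalance, since this imbalance would come from the intervention.

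**Precision.** The 61 records are drawn from all inpatients. A screen-positive subset is smaller, so a power figure computed for 61 does not carry over unchanged.

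Two of the three SBIRT components are affected. At stake are the direction of their estimated effects and the power claimed for them.

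**Working it through.** **Inputs from the article.** 7 v 7 units; 61 records per unit and period; ICC 0.03; 16-point difference; alpha 0.05; 80% power; about one-third positive for drinking or drugs together.

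**Assumed, because not stated.** Two-sided test; base rates; screening rates in each arm; the mix of patients who are screened.

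**Formula.** Effective n per arm = 7m / [1 + (m − 1) × 0.03], where m is the number of records per unit. Power = Φ[(|p2 − p1| − 1.96 × SE0) / SE1], with SE0 from the pooled and SE1 from the unpooled variance.

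**Step 1: the plan's own figure.** At m = 61 the design effect is 1 + 60 × 0.03 = 2.8, and the effective n is 427 / 2.8 = 152.5. For 42% v 58%, the least favourable position for a 16-point difference, power is 80.1%, and 61 is the smallest m that reaches 80%. The total also agrees: 14 × 61 × 3 = 2562. The stated 61 is therefore reproduced as a calculation on all sampled records.

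**Step 2: records left among screen-positives.** With every patient screened in both arms, 61 / 3 ≈ 20 per unit remain for drinking or drugs combined. Each of these alone cannot exceed that number. The article gives no share for tobacco. At m = 20 the design effect is 1 + 19 × 0.03 = 1.57, and the effective n is 140 / 1.57 = 89.2.

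| Records per unit | Rates compared | Power |
|---|---|---|
| 61 v 61 | 42% v 58% | 80.1% |
| 20 v 20 | 42% v 58% | 57% |
| 20 v 20 | 10% v 26% | 80% |
| 20 v 20 | 5% v 21% | 89–90% |
| 4 v 16 (assumed) | 42% v 58% | 29% |
| 4 v 16 (assumed) | 5% v 21% | 45% |

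The 4 v 16 case corresponds to about 20% screened in control units and 80% in toolkit units, with one-third positive: 61 × 0.2 / 3 ≈ 4 and 61 × 0.8 / 3 ≈ 16. The effective n is then 28 / 1.09 = 25.7 v 112 / 1.45 = 77.2.

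**Step 3: direction of bias (all rates assumed, 427 records per arm).**
- Wait-list: 10% screened (about 43), 30 positive, 18 receive BI.
- Toolkit: 80% screened (about 342), 113 positive, 51 receive BI.
- Among screen-positives: 18/30 = 60% v 51/113 = 45%, so the toolkit looks 15 points worse.
- Among all records: 18/427 = 4.2% v 51/427 = 11.9%, so the toolkit is 7.7 points better.

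A second illustration fixes the chance of BI by severity, the same in both arms. Of all patients, 10% are severe users and 23.3% milder; BI reaches 70% and 30% of those who are screened. Control units screen 60% and 10% of these groups, toolkit units 80% of both. Among screen-positives:
- control: (0.10 × 0.6 × 0.7 + 0.233 × 0.1 × 0.3) / (0.10 × 0.6 + 0.233 × 0.1) = 0.049 / 0.083 = 59%
- toolkit: (0.10 × 0.8 × 0.7 + 0.233 × 0.8 × 0.3) / (0.333 × 0.8) = 0.112 / 0.267 = 42%

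Over all records the rates are 4.9% v 11.2%. Selection alone produces the reversal.

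**Step 4: the all-record alternative.** At 61 records per unit, 4.2% v 11.9% has about 70% power (effective n 152.5 per arm). With one-third positive, 80% of them screened and 45% of those given BI, the all-record rate is only 0.333 × 0.8 × 0.45 = 12%. A 16-point gain cannot occur in that setting.

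**The case against.** **The sentence describes data collection, not the model.** This has some force. The endpoint statements carry no screen-positive condition, the Aim 1 section names no subset, and the sentence could be read as the share of all sampled patients who both screened positive and received the service. A condensed article may leave the model denominator to the analysis plan. Still, this is the only place where the article gives BI and RT a denominator, and its plain reading is screen-positives. If all records were meant, one phrase settles it.

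**The power loss is not general.** This stands. A reader might infer that BI and RT simply lack 80% power. The article does not support that: it gives no base rate, and its description of current practice suggests low ones. From 5% or 10%, about 20 records per unit still give roughly 80% to 90% for a 16-point gain. The larger loss depends on a control screening rate that the article describes only in words.

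**The one-third figure leaves out tobacco.** This also stands. It cannot be applied to tobacco or to a combined outcome that includes it.

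**The reversal uses assumed inputs.** True. It supposes that 60% of screen-positive wait-list patients receive BI, and that 30 of about 43 screened (70%) are positive, against one-third in the toolkit arm. If control BI is near zero, a false harm essentially cannot arise. The example shows that a reversal is possible, not how large a bias to expect.

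**All-record percentages have their own weaknesses.** They count patients with no indication as not receiving the component, and Step 4 shows that they do not restore 80% power.

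**Conclusion.** The comparability concern holds. On its plain reading, the article measures BI and RT in a group formed after randomisation by a process the intervention is meant to change, and nothing in the stated intention-to-treat rule or model repairs this. The direction of bias is not known in advance. Reversal of a real gain is possible but rests on assumed rates.

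The power concern holds in a limited form. The 80% for 16 points belongs to outcomes analysed on all 61 records. Among screen-positives for drinking or drugs combined, at most about 20 per unit would be expected at the article's one-third, and fewer where control units rarely screen. Power then runs from 57% (42% v 58%) to about 80–90% (base rates of 10% and 5%) with universal screening, and from 29% to 45% with an assumed 4 v 16 records per unit. All of these figures use ICC 0.03 and a two-sided Z test. The comparability point depends on none of them.

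**What to change.** Before the outcome data are analysed:

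1. For the between-arm tests of BI and RT, use all 61 sampled records per unit as the denominator and documentation of the component as the numerator.
2. Report the percentages among screen-positives as descriptive only.
3. If a narrower supportive denominator is wanted, consider patients positive on the substance-use question asked at admission, provided that it is recorded alike in both arms.
4. Limit the statement of 80% power for 16 points to outcomes analysed on all 61 records. State that all-record differences in BI and RT are likely to be well under 16 points (about 70% power at 4.2% v 11.9%), and give their expected power separately.

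The cost is a change of wording in the protocol and analysis plan; the same records serve. The all-record percentages will be smaller, and they count patients with no indication as not receiving the component, so the report should say so.
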